### Statistical methods

All case–control study analyses will be conducted using conditional logistic regression. Matching factors (i.e. age, area) are controlled for in the design. All statistical analyses will be performed using the statistical software STATA or R.

**CC1.** The *primary objective* of this case–control will be to assess the effect of various measures of attendance at breast screening *strictly prior to* the case’s date of first diagnosis/ the control’s date of pseudo-diagnosis on mortality from primary breast cancer. The primary measure of attendance to screening will be whether a woman ever attended at least one screen episode (indicator variable). Secondary measures will be:

• the total number of screens (counts);

• the time since last screen (continuous variable), and whether that time span fell within the past three years (≤ 3 years or > 3 years), as this corresponds to the NHSBSP protocol and approximates the estimated PCDP;

• the time since penultimate screen (continuous or categorical);

• the interval between last screen and penultimate screen (continuous or categorical);

• the maximum interval between 2 screens (continuous or categorical);

• the average interval between 2 screens (continuous or categorical);

• the patient’s age at first screen (continuous or categorical);

• the patient’s age at last screen.

*Ascertainment, self-selection* and *exposure opportunity* biases will be addressed using the methods described in the *Bias & Effect modification* section.

**
*Secondary objectives*
** will consider time since last screen stratified by age at diagnosis/pseudo-diagnosis, by first tumour detection mode, and by region (Main phase only).

The effect of attending a screen in a particular 3-year age band in the main phase (such as 47–49 inclusive), or 5-year age band in the pilot phase, on mortality from primary breast cancer in the subsequent 5-year age band (such as 50–54) will also be investigated, as performed for the cervical screening audit (Sasieni et al., 2009 [22]). The results of this analysis should be very similar to those obtained from the analysis of “time since last screen” after stratifying the analysis by age at diagnosis/pseudo-diagnosis.

**CC2.** The *primary objective* of this case–control will be to estimate the proportional effects of screening attendance *strictly prior to* date of diagnosis/pseudo-diagnosis and cancer treatment, on prognosis in patients diagnosed with primary breast cancer. The primary and secondary measures of attendance to screening will be as for CC1; in addition, they will include tumour detection mode to assess the relationship between detection mode and choice of cancer treatment.

The regression analysis will be adjusted for tumour attributes such as stage of disease at diagnosis and other pathological features. Because of the extreme collinearity between cancer treatment and pathology variables, e.g. lymph node positivity, a major determinant of treatment choice, estimating relative effects from the regression analysis often gives unreliable/biased estimates of cancer treatment (Wishart et al., 2010 [23]). To address this statistical issue, a counterfactual analysis will be performed (Höfler et al., 2005 [24]). The treatment that an individual actually does not receive is called counterfactual treatment, and the outcome under this treatment, after treatment assignment, is referred to as counterfactual outcome. In our study, the cancer treatment effects will be constrained to the absolute effect estimated from meta-analyses of the RCTs.

*Self-selection*, *lead-time, and length* biases will be addressed using the methods described in the *Bias & Effect modification* section. Because in CC2, both cases and controls have had primary breast cancer, *exposure opportunity* bias can be assumed to be minimal.

**
*Secondary objectives*
** will consider time since last screen stratified by epoch of diagnosis to further explore collinearity among the explanatory variables.

**CC3a/b.** The *primary objectives* of these case-controls will be to estimate the effect attendance at breast screening strictly prior to date of diagnosis/pseudo-diagnosis on incidence of invasive (CC3a) or, of in situ and invasive (CC3b) primary breast cancer, and to estimate rates of overdiagnosis due to screening.

The primary and secondary measures of attendance to screening will be as for CC1, in particular time since last screen; in addition, they will include the patient’s age at last screen, and whether a woman ever missed attendance at recall assessment(s). This last measure should help assess potential room for improvement in the management of suspicious screening results.

With time since last screen, one might expect an observed increase in incidence (excess risk) immediately after a screen (the screen-detected cases), followed by an observed decrease in incidence (deficit in risk) due to the removal of pre-clinical cases by the screen. The deficit would be expected to be attenuated with time since the screen. The analysis will be stratified by age at diagnosis/pseudo-diagnosis. Indeed, one might expect an excess risk of disease in screened ages (within screening age range) and a deficit in risk in non-screened ages (above screening age range); a potential deficit in risk may also be seen at later ages within the screening age range (i.e. at age 65–69 after up to 15 years of screening). In the absence of overdiagnosis, the initial excess risk from screening would be fully compensated by a deficit in risk over time in the absence of screening (“compensatory drop”, Puliti et al., 2011 [16]). The excess risk in screened ages and the deficit in risk in non-screened ages will be quantified and combined with National Incidence Rates to construct risk scores (Field et al., 2005 [25]) in an attempt to estimate lifetime effect of screening on incidence and overdiagnosis. As the NHSBSP has been running for at least 20 years, there should be sufficient follow-up data after screening stopped (age 70), and the method of “compensatory drop” should achieve full adjustment for lead-time (Puliti et al., 2011 [16]). If the pilot phase of the study highlights little or no follow-up after last screen, lead-time bias will be adjusted using the “postponement of screen-detected cases” method (described in the *Bias & Effect modification* section).

The estimations will be performed for all disease (in situ and invasive) and for invasive disease only.

*Self-selection* and *exposure opportunity* biases will be also addressed using the methods described in the *Bias & Effect modification* section.

**
*Secondary objectives*
** will consider time since last screen stratified by region (Main phase only).

**CC4.** The *primary objective* of this case–control will be to estimate the effect of attendance to breast screening *strictly prior to* date of diagnosis/pseudo-diagnosis on incidence of advanced stage primary breast cancer. The primary and secondary measures of attendance to screening will be as for CC1; in addition, they will include age at last screen.

*Self-selection* and *exposure opportunity* biases will be addressed using the methods described in the *Bias & Effect modification* section.

**
*Secondary objectives*
** will consider time since last screen stratified by age at diagnosis/pseudo-diagnosis, and by region (Main phase only). Analysis may be adjusted for stage at diagnosis.

Results from CC1 and CC3 analyses will be combined with published data on breast cancer mortality and incidence over time, respectively, to estimate projected mortality, projected incidence, and stage-specific incidence in the presence and absence of screening and derive prevented fraction as an impact measure to help interpretation and evaluation of the programme benefits harms (Independent UK Panel on Breast Cancer Screening, 2012 [26]).

#### **
*Ethics*
**

The study protocol was reviewed and approved by the UK department of health. Ethical approval was obtained from the London Research Ethics Committee (REC) of the National Research Ethics Service (NRES) (reference number 12/LO/1041), and by the National Information Governance Board NIGB) Ethics and Confidentiality Committee (ECC) (Reference number ECC 6–05 (e)/2012). Both organisations are now merged into the Confidential Advisory Group (CAG).

The study has received from the National Institute for Health Research Clinical Research Network (NIHR CRN) support, and has been provisionally assigned to the National Cancer Research Network (NCRN) (UKCRN Study ID = 14978, http://public.ukcrn.org.uk/search).

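### The maximum and average interval between two screens leave out the gap after the last screen, so on their own these two secondary measures are confounded by time since last screen

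*Protocol article*

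**What the plan says.** All of this stands in the protocol article, Statistical methods.

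- **Primary measure, CC1:** "The primary measure of attendance to screening will be whether a woman ever attended at least one screen episode (indicator variable".
- **Secondary measures, CC1**, in one list of parallel items: "the maximum interval between 2 screens (continuous or categorical", "the average interval between 2 screens (continuous or categorical" and, separately, "the time since last screen (continuous variable), and whether that time span fell within the past three years". The three-year cut is justified "as this corresponds to the NHSBSP protocol and approximates the estimated PCDP". Number of screens, time since penultimate screen and age at first screen are also listed.
- **History window:** only attendance strictly before the case's first diagnosis, or the control's pseudo-diagnosis date, counts. That date is not a screen, so it cannot close an interval.
- **Re-use:** for CC2 and CC4, "The primary and secondary measures of attendance to screening will be as for CC1"; CC3a/b takes the CC1 measures over in the same way.
- **Time dependence, CC3a/b:** after the initial excess at screening, incidence falls, and "The deficit would be expected to be attenuated with time since the screen".

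The article does not say that the interval measures are adjusted for, or modelled jointly with, time since last screen.

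**The concern.** An interval between two screens needs an attended screen at both ends. A woman who attends twice on time and then stops has one closed interval of three years, and nothing after it enters the maximum or the average. She is scored as a regular attender. Yet by the article's own reasoning, which ties three years to the programme and to the pre-clinical detectable period, she is among the less protected.

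The reference group with short intervals is then a mixture of regular attenders and women who gave up. If the second group has the higher risk, the contrast between long and short intervals is pulled down. That affects mortality in CC1, and fatality and advanced-stage incidence where the measures are re-used in CC2 and CC4. The size of the main phase does not help, because it only tightens the confidence interval around a confounded estimate.

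**Working it through.** The article gives no figure to reproduce here. The check has three steps.

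**1. Scoring three records (no rates assumed).** Reference age 69; the programme interval of three years is from the article.

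| Screens at age | Closed maximum | Closed average | Open gap | Maximum with open gap |
|---|---|---|---|---|
| 50, 53 | 3 | 3/1 = 3 | 69 − 53 = 16 | 16 |
| 50, 53, 56, 59, 62, 65, 68 | 3 | 18/6 = 3 | 1 | 3 |
| 50, 53, 59, 62, 65, 68 | 6 | 18/5 = 3.6 | 1 | 6 |

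Under the stated definition, the woman unscreened for 16 years ties with the perfect attender and ranks above the woman who missed one round.

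**2. When does the contrast reverse?** Give regular attenders risk 1, lapsed women r_L, and women with a past long gap who returned r_I. If lapsed women make up a share f of the short-maximum group, that group's mean risk is 1 + f(r_L − 1). The long-interval group looks protected when

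f > (r_I − 1)/(r_L − 1).

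The article's sample-size odds ratio of 0.7 for ever attending gives r_L = 1/0.7 = 1.43, if a lapsed woman loses all protection (an assumption). The values of r_I are also assumed.

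- r_I = 1.1: 0.1/0.43, so f above 23%.
- r_I = 1.2: 0.2/0.43, so f above 47%.
- With r_L = 1.2 the thresholds are 50% and 100%; with r_L = 1.8 they are 13% and 25%.

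Below the threshold the effect is attenuated, not reversed.

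**3. Simulation.** The article gives no attendance or lapse rates, so all rates are assumptions.

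*Matched sets.* 9,000 sets (1 case, 2 controls), ages 57–71, three-yearly invitations, 90–92% attendance per round while active, odds ratio 0.6 for a screen in about the last three years, no separate risk from past gaps.

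| Lapse per round | Odds ratio per extra year, closed maximum (95% CI) |
|---|---|
| 3% | 0.970 (0.947–0.992) |
| 6% | 0.981 (0.954–1.008) |
| 10% | 0.957 (0.930–0.984) |

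The closed average gave 0.967–0.997. A maximum that counts the open gap gave 1.041–1.063, with every interval above 1. With no screening effect, the closed maximum gave 0.997 and the open-gap version 1.014.

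*Population model.* 600,000 women per scenario, ages 56–70, at least two screens, age-adjusted logistic regression in place of the matched model. Log-odds of death rise by 0.07 or 0.12 per year since last screen beyond three years; past gaps carry no risk of their own.

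| Assumed share of lapsers | Odds ratio, closed maximum > 3.5 years |
|---|---|
| 0% | 1.02–1.04 |
| 10% | 0.92–0.93 |
| 20% | 0.81–0.93 |
| 30% | 0.73–0.89 |
| 40% | 0.71–0.81 |

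With at least 10% lapsers:

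- 86–98% of women with an open gap over 3.5 years had a closed maximum of 3.5 years or less;
- the closed average gave 0.87–0.98 per year;
- counting the open gap gave 1.19–1.88 for the maximum;
- keeping the closed maximum and adjusting for time since last screen gave 0.95–1.04.

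In this model a past gap has no effect given time since last screen, so the adjusted value should be near 1, and it is.

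*Past gaps with and without their own risk.* A further run with 3–10% lapse per round gave 0.95–0.98 per year for the closed maximum when past gaps carry no risk. When they do, the result was mainly attenuation, for example 1.02 against 1.05 after adjustment. With time since last screen in the model, the estimate was about 0.98–1.00 in the first case and the unattenuated value in the second.

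**The case against.** The strongest reply is that the list measures separate dimensions of history separately. Closed intervals describe spacing among attended screens, while lapse is captured by time since last screen and by the number of screens. The secondary objectives of all the studies are built on time since last screen. This stands: the lapsed woman is not lost from the analysis as a whole. It does not remove the confounding when the maximum or average is read on its own, and no joint model is stated.

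Other parts of the reply also stand.

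- **Invented rates.** The sizes rest on assumed lapse and attendance rates. The models in which past gaps carry no risk favour reversal, one of the three matched-set intervals includes 1, and without lapsers no reversal appeared. The simulated ages (56–71) are narrower than the case range of 47–89.
- **Purpose.** The article does not say that these two measures will decide the screening interval. A reader might infer that from its reference to the cervical evaluation, but it is an inference.
- **CC3.** Excess incidence is expected just after a screen and a deficit later, so long gaps have no simple expected direction there and reversal has no clear meaning.
- **Women with no screen or one screen.** A reader might infer that their matched sets are dropped. The article allows categories, and the coding may sit in the full plan, so this is not a finding.

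**Conclusion.** The point holds in a limited form. As defined, the two interval measures score women who stopped after two or more on-time screens as regular attenders. Analysed alone, they are confounded by time since last screen. The scoring fault follows from the wording and needs no assumed rates.

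The size does need them. At 3–10% lapse per round the distortion is modest, around 2–5% per extra year of maximum interval. It is larger in the population model, where the assumed lapser share reaches 40%.

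A reader might infer that the interval effect will come out reversed. The documents do not support that: attenuation is the safer expectation where past gaps matter in their own right, and reversal needs enough lapsed women in the reference group. Nor does a woman who stops always look regular. One who was irregular before stopping keeps her long maximum, and one with a single screen has no interval. The concern covers CC1, CC2 and CC4. The primary ever-attended analysis is untouched.

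**What to change.** - Fit the maximum and the average interval each in the same conditional logistic model as time since last screen, which is already a planned variable. Apply this in CC1, CC2 and CC4, and state no simple expected direction for CC3a/b.
- In addition, or instead for the maximum, add a version that counts the gap from last screen to (pseudo-)diagnosis. Truncate it at the end of the invitation age range, since cases run to age 89 while the article puts the end of screening at 70 ("there should be sufficient follow-up data after screening stopped (age 70"). Give never-screened and one-screen women their own categories.
- Keep the closed average, adjusted for time since last screen. Do not replace it with eligible time since first screen divided by number of screens. At reference age 69 that scores a late starter screened at 65 and 68 as 4/2 = 2.0 and a seven-screen lifelong attender as 19/7 = 2.7, so the late starter looks better screened.

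The cost is a little more analysis work; screen dates are already among the variables in Table 1. The open-gap maximum overlaps with time since last screen and should be interpreted beside it.

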### Participants: selection of cases & controls

#### **
*CC1 & CC2*
**

*Population of dead cases (A)* All women who died of primary breast cancer (as stated in part 1 of the death certificate) age 47–89, within the specified 2-year study period will be selected. Cases of women with only in situ primary breast cancer records (i.e. no invasive record) will be included, but Death Certificate Only (DCO) cases will be excluded. Case A women will have had their date of first diagnosis of primary breast cancer (in situ or invasive) age 47–89 and since 1990, and for subsequent phases of this evaluation (main phase onwards), they will not have been included as cases in previous evaluation periods, although they may have been included as controls, and may also be selected as a case C in the same evaluation.

*Population of cases A-matched general population controls (B)* For each case A, two women will be selected among the general population in the Health & Social Care Information Centre (HSCIC) database at Exeter who, are registered in the same National Health Applications and Infrastructure Services (NHAIS) system as the case at the case’s date of first diagnosis, are alive at the case’s date of death, and were born within 1 month either side of the case’s date of birth. Control B women may have had primary breast cancer (in situ or invasive) at the case’s date of first diagnosis. For subsequent phases of this evaluation (main phase onwards), they will not have been included as population controls B, E, or D in previous evaluation periods, although they may be included as a controls E or D within the same evaluation period.

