**For CC4**, incident cases (C) will be restricted to those women with advanced stage (defined below) primary breast cancer, and matched general population controls (D) will be restricted to those women who have never had advanced stage primary breast cancer, but may have had in situ or early stage primary breast cancer prior to *and including* the case’s date of index diagnosis. Breast cancer will be defined as “advanced stage” if tumour size is larger than 20 mm, or if at least one regional lymph node is affected, or if both, and as “early stage” if tumour size is equal to or smaller than 20 mm and no regional lymph node is affected. For the purpose of data collection, we have used an inclusive definition of “advanced stage”, but we will also analyse the data by Stage to assess the association between screening and metastatic breast cancer for instance, and using only those cases which are node positive, as this is generally accepted as an important prognostic factor and as a predictor of the effect of screening on mortality (Smith et al., 2004 [10]).

If no matched control is found for a particular case (A or C) with a date of birth within 1 month either side of the case’s date of birth, the range will be expanded to 3 months either side (or 6 months either side if the case’s age at index diagnosis of primary breast cancer is under 50 or over 70).

All cases and controls will appear on the HSCIC database at Exeter. We will aim to select female cases and controls who have been registered with the NHS by age 47 (determined by either date of first registration on local NHAIS system or prior cervical/bowel screening history), and have had available data on both breast and cervical (for women aged 47–64), and, possibly bowel (for women aged 60–69) screening strictly prior to their date of first diagnosis/pseudo-diagnosis (that is, they have been invited to screening at least once), although this may not be practicably feasible for dead cases and matching controls with older age at death. Patient breast, cervical, and bowel (for the main phase) screening history, primary breast tumours attributes and treatment data will be retrieved for all cases and controls, as well as deprivation quintile.

A detailed description of the algorithm to be used for the selection of cases and controls is available from the authors.

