Once diagnosed with breast cancer, the cases come under clinical management and do not continue with routine breast screening as before. The controls, however, may continue to attend screening up to the time of the case being entered into the study. This potential bias is addressed at the design stage by giving the controls a pseudo-diagnosis date that is the same as that of their matched case and screening history is only considered up to that date (Connor et al., 2000 [14]). This is in fact an over-correction and results in a bias *against screening*. The fact of the case having necessarily a diagnosis of breast cancer and a control usually not having such a diagnosis, induces an artificially higher retrospective probability of screening exposure in the cases, a bias *against screening* (i.e. the screen-detected cases will always have this screen recorded at diagnosis, whereas the large majority of controls will not at pseudo-diagnosis). Simply excluding the detection screens from the histories would bias the results *in favour of screening*. When assessing the effect of ever having been screened, the major driver of this bias is prevalence screening, and for a mature programme with approximately 6 incidence screens for each prevalence screen, this bias is likely to be small. However, this bias may remain when using other measure of screening exposure. The extent of screening opportunity bias will be investigated by applying an analytical correction to the odds ratio using the method by Duffy et al., 2008a [15], and by performing sensitivity analyses in which the date of pseudo-diagnosis for controls will be extended by up to 4 years, the estimated average sojourn time for each screen-detected case, to counteract the artificially higher retrospective probability of screening exposure in cases (Connor et al., 2000 [14]).

But the major sources of bias in case–control studies are potential self-selection and lead-time biases (Puliti et al., 2011 [16]). Length bias will also be discussed. Note that lead-time and length biases will only affect analyses assessing the effect of screening on survival among cases (i.e. case-study 2), but not those assessing its impact on population outcomes (incidence or mortality).

#### **
*Self-selection bias (or non-compliance bias)*
**

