The extreme form of length bias is overdiagnosis, defined as the diagnosis of cancers which would not have come to clinical attention in the patient’s lifetime had screening not taken place. Overdiagnosis can be estimated by comparing cumulative incidence in screened and unscreened populations several years after screening stops (Biesheuvel et al., 2007 [21]). Estimates of overdiagnosis obtained from observational studies vary widely according to the design used, i.e. dynamic populations or cohort populations (Puliti et al., 2011 [16]). In case–control studies, which are nested within a cohort population, overdiagnosis can be robustly estimated provided that (1) the difference in underlying risk of primary breast cancer between screened and unscreened populations (i.e. self-selection bias), and (2) the period of time by which the diagnosis is brought forward by screening (i.e. lead-time bias) are both accounted for (Duffy et al., 2010 [13], Puliti et al, 2011 [16]). In the absence of overdiagnosis, the initial increase in primary breast cancer occurrence in the screened group would be fully compensated by a similar decrease in cancers among older age groups no longer offered screening (“compensatory drop method”, Puliti et al., 2011 [16]).

In addition to investigating the extent of the different biases when examining the relationship between screening and mortality or incidence, identifying homogeneous strata that may (positively or negatively) modify the effect of the screening exposure on the outcome (effect modifiers), such as age at diagnosis / pseudo-diagnosis (5-year band), epoch of diagnosis (5-year band), and tumour detection mode of the cases will be of interest.

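### CC1 strata by the case's detection mode cannot be read as effect modification against population controls, and the optional CC4 stage adjustment is either inestimable or without effect

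*Protocol article*

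**What the plan says.** **CC1.** Under Statistical methods, the CC1 secondary objectives "will consider time since last screen stratified by age at diagnosis/pseudo-diagnosis, by first tumour detection mode, and by region (Main phase only"). Under Bias & Effect modification, the list of effect modifiers closes with epoch of diagnosis "and tumour detection mode of the cases will be of interest". This makes clear whose detection mode is meant and that it is sought as a modifier of the screening effect.

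Controls B are drawn from the general population register. The selection section allows that "Control B women may have had primary breast cancer (in situ or invasive"), but does not require it, and the legend to Figure 1 says most general-population women have not had cancer.

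**The link between detection mode and exposure.** In the paragraph on exposure opportunity bias the protocol observes that "the screen-detected cases will always have this screen recorded at diagnosis, whereas the large majority of controls will not at pseudo-diagnosis". It adds that simply leaving detection screens out would bias results in favour of screening.

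**CC4.** The CC4 secondary objectives end with "Analysis may be adjusted for stage at diagnosis". In the selection section, "incident cases (C) will be restricted to those women with advanced stage (defined below) primary breast cancer", while controls D must have "never had advanced stage primary breast cancer, but may have had in situ or early stage primary breast cancer". The same section separately plans analyses by stage and in node-positive cases.

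**The concern.** An effect modifier has to be defined for both members of a matched set, or at least must not be determined by the exposure. The case's detection mode fails on both counts in CC1. Most controls B have no detection mode. A case is screen-detected only if she has just been screened, and the symptomatic cases are what is left once those recently screened women are removed. Comparing either group with unselected controls conditions on part of the exposure.

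The likely result is a table showing apparent benefit in women with symptomatic cancers and apparent harm in women with screen-detected cancers, with neither telling the reader anything about screening. This is a recurring national evaluation meant to inform policy, so such a table could mislead.

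The CC4 sentence is a different and smaller fault. Stage is part of the definition of the CC4 outcome, so it cannot also serve as an adjustment covariate.

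**Working it through.** The plan gives no figure for the detection-mode strata or for the stage-adjusted CC4 model, so there is nothing of its own to reproduce here.

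**1. CC1, recent screening as exposure, detection screen counted, no true effect.**

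Inputs, both assumed because the protocol does not state them:
- 70% of controls screened within the past three years
- a share s of all cases screen-detected, from 10% to 40%

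Under no effect, cases overall are also 70% exposed. All screen-detected cases are exposed. The exposed proportion x among the remaining cases satisfies

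0.70 = s + (1 - s)x, so x = (0.70 - s)/(1 - s).

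The exposure odds in symptomatic cases are x/(1 - x) = (0.70 - s)/0.30. Dividing by the control odds 0.70/0.30 gives

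OR (symptomatic sets) = (0.70 - s)/0.70 = 1 - s/0.70.

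| s | x | OR, symptomatic sets |
|---|---|---|
| 0.10 | 0.667 | 0.86 |
| 0.20 | 0.625 | 0.71 |
| 0.30 | 0.571 | 0.57 |
| 0.40 | 0.500 | 0.43 |

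In the screen-detected sets every case is exposed, so the odds ratio is unbounded. The unstratified odds ratio is 1.00 throughout.

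**2. The same point by conditional logistic regression.** 200,000 simulated 1:2 sets used 77% attendance in controls (the protocol's coverage figure for ages 53–70, which it does not give as a design input). Let q be the share of attending cases that are screen-detected, assumed 0.30, 0.45 or 0.60.
- No true effect: symptomatic sets gave 0.70, 0.55 and 0.40, i.e. 1 - q. Screen-detected sets diverged.
- True odds ratio 0.7: symptomatic sets gave 0.49, 0.38 and 0.28, i.e. about 0.7(1 - q).

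The two calculations agree: s = 0.30 with 70% attending is q = 0.30/0.70 = 0.43, and 1 - 0.43 = 0.57.

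**3. CC1, only earlier screens counted, no true effect.** Assume 77% current attendance, q = 0.45, earlier attendance in 90% of current attenders and in 35% of current non-attenders.
- Controls: 0.77 × 0.90 + 0.23 × 0.35 = 0.7735, odds 3.415.
- Screen-detected cases: 0.90, odds 9. OR = 9/3.415 = 2.6.
- Symptomatic cases: (0.77 × 0.55 × 0.90 + 0.23 × 0.35)/(1 - 0.77 × 0.45) = 0.4617/0.6535 = 0.706, odds 2.406. OR = 2.406/3.415 = 0.70.

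With 95% in place of 90%, the same steps give 4.4 and 0.65. The simulation gave 2.6 to 4.3 and 0.71 to 0.66. The distortion becomes finite but keeps its direction.

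**4. CC4.** Every case has an advanced stage and every control has no stage or a lower one. In a conditional likelihood an individual stage term then identifies the case in each set perfectly. In 1,400 simulated 1:2 sets the standard error of the screening log odds ratio was 0.074 without stage and about 9 with it, and the log-likelihood went to nearly zero, which is the mark of complete separation. Giving 1% of controls early-stage disease did not help (standard error 6.4). If the case's stage is instead assigned to the whole set, it is constant within the set and its main effect drops out, leaving the screening odds ratio unchanged.

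**The case against.** Five points can be made for the protocol.

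**It knows the mechanism.** The exposure opportunity paragraph describes it, warns that it may persist for measures other than ever having been screened, and plans an analytical correction and an extension of the control's pseudo-diagnosis date by up to four years. This is true, but those methods are aimed at the overall odds ratio and nothing applies them within detection-mode strata. As written, the extension is tied to screen-detected cases, so it would not repair the symptomatic sets. The caveat under Ascertainment bias on time since last screen in screen-detected patients concerns overdiagnosis only.

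**Exposure is defined as screening before diagnosis.** A reader might infer that the screen-detected stratum always gives an infinite odds ratio. The document does not support that. It restricts exposure to screens strictly before diagnosis, yet discusses both including and excluding the detection screen. If the detection screen is left out, the excess is finite (step 3). Time since last screen is also to be analysed as a continuous variable, for which the figures above are only illustrative.

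**The inputs are assumptions.** This stands. Cases A are aged 47–89 and include women past screening age, so s could be low. At 10% the symptomatic odds ratio is 0.86, a mild distortion.

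**CC4 is different.** A reader might infer that stage adjustment yields a spurious CC4 estimate and undermines the check on the mortality result. Neither follows. The adjusted model gives no usable estimate or the same estimate, and the sentence is permissive and sits under secondary objectives. The primary CC4 analysis is not stage-adjusted, and the planned analyses by stage and in node-positive cases are ordinary outcome-subtype comparisons.

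**Scope.** The CC3 and CC4 secondary objectives name no detection-mode stratification; only the general sentence on effect modifiers could reach them. Nor is it strictly true that controls lack these variables: some controls B may have had breast cancer, and some CC4 controls may have in situ or early-stage disease.

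**Conclusion.** The point holds for CC1 in a limited form. Detection-mode strata against population controls do not estimate effect modification, because the stratifier is partly defined by the exposure and most controls have no value for it. With no true effect, symptomatic sets fall below 1 (0.86 to 0.43 under the stated assumptions) and screen-detected sets rise above 1, by an amount that depends on whether the detection screen counts. The sizes rest on assumed screening and detection shares. Under the step 1 model the direction holds for any screen-detected share above zero; in step 3 it also requires earlier attendance to be commoner in current attenders. The primary CC1 odds ratio, ever attended versus never, is not stratified this way and is unaffected.

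For CC4 the stage adjustment is unusable rather than misleading, and the primary CC4 comparison stands. Both items are secondary or optional, but both are worth correcting before analysis.

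**What to change.** - **CC1 secondary objectives:** remove first tumour detection mode as a stratifier of time since last screen. Keep age and region.
- **Effect modification paragraph:** state that detection mode is not used as an effect modifier in comparisons with general-population controls.
- **Where to examine detection mode:** in CC2, which already lists it among its measures and where both members have a tumour, with the lead-time and length-bias methods planned there; or descriptively among cases only.
- **CC4 secondary objectives:** delete the sentence allowing adjustment for stage, and refer to the by-stage and node-positive case analyses already planned in the selection section.

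The cost is one secondary stratification and one optional adjustment. The changes are to wording only: no new data, no change to sample size, and no change to any primary analysis.
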